## Background

Acute myeloid leukemia (AML) is predominantly a disease of older patients for whom the prognosis is still poor [1, 2]. Intensive induction chemotherapy, usually consisting of an anthracycline and cytarabine, induces remission in about 50% of older fit patients, but most of these patients relapse and still succumb to their disease. Disease-related factors such as the genetic profile of the disease predict resistance to current standard therapy [3]. In line, the proportion of patients with a high-risk disease profile according to European LeukemiaNet (ELN)-2017 risk classification [4] increases with older age to roughly one-quarter of patients 70 years or older [5]. Combination of an anthracycline with cytarabine remains the standard of care of intensive induction therapy in patients considered medically fit [1, 2, 4] and the proportion of patients receiving intensive chemotherapy even in older patients is high with 80% to 90% in 60- to 70-year-old patients and 50% to 75% in patients aged between 70 and 75 years [5]. For patients who achieve a complete remission (CR) after induction chemotherapy, post-remission therapy is required to prevent relapse. However, despite intensive consolidation therapy, overall survival in older (≥ 60 years) patients remains poor with less than 10% being alive after 5 years [6]. Beyond age, genetic abnormalities constitute the most influential prognostic factors for survival [7, 8]. This is reflected in the current World Health Organization (WHO) classification of myeloid neoplasms and acute leukemia [9].

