### Efficacy

The GnG trial has two efficacy endpoints. The first is MRD-negativity after sequential or single-dose GO in combination with intensive induction therapy. MRD-negativity is defined as the absence of leukemic cells at the end of the induction therapy assessed by flow cytometry with a sensitivity of 10^-4-^10^-5^. If MRD-negativity cannot be measured, or if patients drop out of the study before MRD measurements, missing values will be replace using multiple imputation. Patients who die from any cause before MRD measurement will be regarded as MRD-positive. The second endpoint is EFS after two years; EFS is defined as the time from randomization until one of the following events, whichever occurs first: a) failure to obtain CR or CR with incomplete neutrophil or platelet recovery (CRi) after induction therapy, b) relapse from CR/CRi or c) death from any cause. Patients without an event are censored at last follow-up. Refractory disease or treatment failure is defined as failure to achieve CR or CRi, presence of Auer rods, or appearance of new or worsening extramedullary disease after induction therapy. Relapse after CR or CRi is characterized by ≥5% blast cells in the bone marrow aspirate and/or biopsy not attributable to any other cause, the reappearance of leukemic blasts in the peripheral blood, appearance of extramedullary leukemia, or presence of Auer rods. Platelet (≥100 G/l) and neutrophil (≥1.0 G/l) counts for the assessments of CR and CRi are assessed according to standard criteria [4].

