### Sample size calculation and statistics

Addressing two primary endpoints, MRD-negativity after induction therapy and EFS, 252 evaluable patients are needed to reject each of the two null hypotheses at a two-sided significance level of 2.5% with a power of at least 85%.

The first primary endpoint evaluation involves the comparison of rates of MRD-negativity assessed by flow-cytometry after induction therapy between GO-147 and GO-1. Assuming a rate of MRD-negativity of 45% for GO-147 and 20% for GO-1, as well as a 3% dropout rate, a total number of 252 evaluable patients are needed to reject the null hypothesis of no difference regarding the MRD-negativity rate for patients receiving GO-147 as compared to patients receiving GO-1 during induction therapy at a two-sided significance level of 2.5% with a power of at least 85% using a chi-squared test.

The second primary endpoint evaluation involves a two-group comparison of EFS between the experimental arm of glasdegib as well as the control arm of placebo both as adjunct to standard consolidation therapy. Assuming a 2-year EFS of 38.5% for the experimental arm and a 2-year EFS of 21% for the control arm (resulting in a hazard ratio of HR=0.612), as well as an exponentially distributed dropout rate of 5% at 2 years, a total number of 224 evaluable patients (based on a number of *d*=178 required events) are needed to reject the null hypothesis assuming no difference regarding EFS for patients receiving glasdegib as compared to patients receiving placebo at a two-sided significance level of 2.5% with a power of at least 85% using a log-rank test, assuming an accrual time of 24 months, as well as a follow-up time of 24 months. This leads to a total sample size of N=max(252, 224)=252 patients to be enrolled for the whole trial to ensure a power of at least 85% for both primary endpoints.

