The MRD-negativity after induction therapy is analyzed using a generalized linear mixed model and EFS with a Cox regression frailty model. Both models are adjusted for the following fixed factors: treatment (MRD-negativity: GO-1 vs. GO-147 and EFS: glasdegib vs. placebo), age, sex, and ECOG PS, as well as for the random factor “recruiting center”. The primary analysis is based on the full analysis set including all randomized patients. Adjustment for multiple testing is done using the Bonferroni-Holm procedure in order to control the family-wise error rate at a two-sided significance level of 5% in the strong sense. Missing values for the short-term primary endpoint MRD-negativity are replaced using multiple imputation by using the fully conditional specification method [39]. Odds and hazard ratios are reported alongside with two-sided 97.5% and 95% confidence intervals, and a possible center effect is assessed by calculating the intra-class correlation coefficient and by presenting the results stratified for the center. A sensitivity analysis of the long-term primary endpoint additionally includes the interaction between maintenance therapy and induction therapy. Statistical analysis is performed using SAS v9.4 or higher.

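### The EFS power of at least 85% rests on one hazard ratio of 0.612 from randomisation, although events before consolidation cannot respond to glasdegib; it needs an unstated, stronger post-remission effect

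*Protocol article*

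**What the plan says.** The section on sample size and statistics fixes the EFS effect as follows: "Assuming a 2-year EFS of 38.5% for the experimental arm and a 2-year EFS of 21% for the control arm". It converts these two rates into a single effect measure, "resulting in a hazard ratio of HR=0.612". From this it obtains "178 required events" and "a total number of 224 evaluable patients"; the operating characteristics are given as "at a two-sided significance level of 2.5% with a power of at least 85% using a log-rank test", with 24 months of accrual, 24 months of follow-up and 5% exponential dropout at 2 years. Enrolment is 252, set by the MRD endpoint. The analysis population is broad: "The primary analysis is based on the full analysis set including all randomized patients".

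The Efficacy section starts the clock early: "EFS is defined as the time from randomization until one of the following events, whichever occurs first". The first listed event is failure to reach CR or CRi after induction; death from any cause also counts. Under Study setting and randomization, both assignments are made upfront. Glasdegib or placebo is given with consolidation and then as maintenance, not during induction (Consolidation and maintenance therapy). Patients without CR/CRi after induction are withdrawn (Withdrawal of patients). The only remission rate in the article is in the Background, where intensive chemotherapy "induces remission in about 50% of older fit patients".

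**The concern.** An induction failure, or a death before consolidation, is an EFS event that precedes the first dose of glasdegib or placebo. Assignment to glasdegib cannot change its probability. The hazard ratio is therefore 1 in the first phase and something else afterwards, whereas the calculation applies 0.612 throughout.

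Two things are at stake. The effect that glasdegib must achieve in the patients who receive it is larger than 0.612 suggests, and a reader cannot see how large. And the power figure comes from a model that does not match the design. If EFS is negative, the stated 85% would make that result look more informative about glasdegib than it may be.

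**Working it through.** **Step 1: the plan's own figures reproduce.** Inputs are those of the sample size section.

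- HR = ln(0.385)/ln(0.21) = 0.9545/1.5606 = 0.6116.
- Events (Schoenfeld, 1:1) = 4 × (2.2414 + 1.0364)² / (ln 0.6116)² = 42.98/0.2417 = 177.8, so 178.
- With exponential EFS and the stated accrual, follow-up and dropout, the event probability is 0.872 (placebo) and 0.730 (glasdegib), mean 0.801. Patients = 178/0.801 = 222, against 224 stated.
- At 252 patients: about 202 events and power Φ(0.4917 × √201.9/2 − 2.2414) = Φ(1.25) = 89%.

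The arithmetic is sound under exponential curves and proportional hazards from day 0.

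**Step 2: the model against the design.** The exponential control curve has hazard −ln(0.21)/24 = 0.0650 per month. It implies 1 − exp(−0.0650 × 1.5) = 9% of events by 1.5 months, about the end of the day 28 to 42 marrow window. A 50% remission rate would imply up to about half of patients with an early event.

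**Step 3: the post-remission effect implied by the stated rates.** Let c be the proportion reaching remission, equal in both glasdegib arms because no study drug has been given. Then 2-year EFS = c × (2-year event-free proportion among remitters), and the required post-remission HR = ln(0.385/c)/ln(0.21/c). The values of c are an assumed range, because the article gives no expected rate for this trial.

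| c | Remitters event-free at 2 years, glasdegib vs placebo | Required HR |
|---|---|---|
| 50% | 77% vs 42% | 0.30 |
| 60% | 64% vs 35% | 0.42 |
| 70% | 55% vs 30% | 0.50 |
| 80% | 48% vs 26% | 0.55 |

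**Step 4: power by log-rank simulation** (252 patients, control 2-year EFS 21%, stated accrual, follow-up and dropout, no treatment effect on early events). With no early failures the check returns 87–89%, in line with Step 1. Separate simulation runs agree to within about 3 points.

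| c | 38.5%/21% met, failures over days 28–42, α 2.5% | Same, α 5% | HR only 0.612 after remission, α 2.5% |
|---|---|---|---|
| 50% | 67% | 76% | 18–27% |
| 60% | 71% | 79% | 32–40% |
| 70% | 78% | 85% | 47–53% |
| 80% | 83% | 89% | 64–68% |

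If all failures are dated on one day, power with 38.5%/21% met is about 82–85% at α 2.5%. At 90% remission it is 86–88%. The ranges in the last column span both dating conventions.

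**Why dating matters.** The log-rank variance for D tied events among n at risk carries the factor (n − D)/(n − 1). With 126 of 252 failing on one day, this is 126/251 = 0.50, so those events contribute about half the noise they would add if dated separately.

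**The case against.** The strongest reply is that 38.5% and 21% are stated as EFS by arm, on an endpoint that already includes induction failure. The article never says that 0.612 is the effect among remitters. A reader might infer that the design simply lacks its stated power, or point to the lowest figures above. The documents do not support that as a flat statement: the lowest figures come from moving 0.612 onto remitters, and the 82–85% figures arise if the stated rates hold and failures share one date. What stands is that the stated rates then need a stronger post-remission effect, which the article neither states nor justifies.

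The 50% remission rate is a background figure, not a design input. GO, or the permitted HAM cycle if remission after it counts, could raise it. A reader might infer that half of all patients fail before glasdegib can be given; the article does not establish that, so only a range is defensible.

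Bonferroni-Holm lets EFS be tested at 5% once MRD is rejected. Under the plan's 45% versus 20%, with 126 per arm, MRD power at 2.5% is about 98%. This narrows the practical shortfall, largely removing it from 70% remission upwards. The article's own claim, however, is made at 2.5%.

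Finally, relapse-free survival from CR/CRi is already a secondary endpoint, so a negative EFS result would not be uninterpretable.

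**Conclusion.** The concern holds in this form: the claim of at least 85% EFS power comes from a constant-hazard-ratio model that the design contradicts, and it depends on a post-remission effect that is not stated. That effect is about 0.30 to 0.55 for remission rates of 50% to 80%, against the 0.612 shown. If the 2-year rates are met exactly, power at two-sided 2.5% runs from about 67% to 83% with failure dates spread over days 28 to 42, and is about 82–85% with a single date. At 90% remission the claim is met. If the post-remission hazard ratio is only 0.612, power is about 18% to 68% across the same remission range.

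These figures assume equal remission rates in the two glasdegib arms, a constant hazard ratio after remission, and no effect before it. Deaths in remission before consolidation, and maintenance postponed by transplantation, are not modelled and could dilute the effect further.

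**What to change.** In the sample size section:

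1. State the expected CR/CRi rate and the post-remission hazard ratio assumed for glasdegib.
2. Recompute EFS power under a two-phase model, with a hazard ratio of 1 before consolidation and the stated value afterwards, and say how failures are dated. Show a range of remission rates, at 2.5% and at the 5% that Holm allows after MRD is rejected.
3. Drop the claim of at least 85% wherever the recomputed figure does not reach it.

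This is a change of text and one recalculation, best made before unblinding. It needs no new data and no change in enrolment. The cost is a less favourable stated power.

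Optionally, name the planned relapse-free survival analysis from CR/CRi, by assigned glasdegib arm, as the key supportive analysis for interpreting a negative EFS result. Replacing EFS as the primary endpoint is a separate design judgement and not part of this fix: recruitment has begun, it would change the estimand, and the claim would be limited to patients who reach remission.

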Gemtuzumab ozogamicin (GO) is a humanized immunoglobulin G4 antibody (hP67.6) directed against CD33 and conjugated to the DNA toxin calicheamicin via a hydrolyzable linker. GO/CD33 complexes are internalized into lysosomes, releasing calicheamicin and promoting single and double-strand breaks hereby inducing cellular death [10]. GO initially received accelerated FDA approval in 2000 for the treatment of patients aged ≥60 years with CD33 positive AML in first relapse [10]. Thereafter, a phase 3 study (S0106) was conducted by the Southwest Oncology Group (SWOG) in untreated de novo AML patients, comparing daunorubicin/cytarabine (DA) with 45 mg/m^2^ daunorubicin plus GO 6 mg/m^2^ on day 4 versus DA alone with 60 mg/m^2^ daunorubicin. The GO arm showed higher induction mortality (5.5% vs. 1.4%), without improving CR or relapse-free survival [11]. Based on these negative results, GO was withdrawn from the market in 2010. Meanwhile, results from five additional randomized studies with GO as adjunct to intensive induction therapy are available: Groupe Ouest Est d’Etude des Leuce´ mies aigue¨s et Autres Maladies du Sang (GOELAMS) AML2006IR [12], Medical Research Council (MRC) AML15 [13] and ALFA-0701 [14, 15], National Cancer Research Institute (NCRI) AML16 [16], and German-Austrian Acute Myeloid Leukemia Study Group (AMLSG) 09-09 [17]. ALFA-0701 randomized 278 patients aged 50 to 70 years with untreated de novo AML to either DA (60 mg/m^2^ daunorubicin) alone or to the same in combination with a fractionated GO induction schedule (3 mg/m^2^ on days 1, 4, and 7) [14]. Although CR with or without platelet recovery and early deaths were similar, patients in the GO arm had significantly improved median event-free (19.6 vs. 11.9 months; *P*=0.00018) and overall survival (OS) (34 vs. 19.2 months; *P*=0.046). A subgroup analysis revealed that the clinical benefit is mainly restricted to patients with favorable and intermediate-risk karyotype [14]. A meta-analysis of 3.325 patients (aged 18–84) from 5 randomized studies investigating GO as adjunct to induction chemotherapy in untreated AML concluded that the addition of GO improved OS in patients without adverse cytogenetics [18]. Rates of sinusoidal obstruction syndrome (SOS), a side effect associated with GO treatment, and 30- and 60-day mortality were lower with 3 mg/m^2^ vs. 6 mg/m^2^ GO [19]. Out of the five studies included in the meta-analysis, Castaigne et al. was the only one reporting on fractionated GO in a dosage of 3 mg/m^2^ on days 1, 4, and 7 (GO-147) [14, 18]. Interestingly, the addition of GO to induction therapy did not lead to an improved CR rate but a significantly higher rate of patients being negative for measurable residual disease (MRD-negative, 7% versus 39% in the standard and experimental arm, respectively) [20]. In addition, treatment with fractionated GO-147 was associated with a significant survival benefit in the large meta-analysis in comparison to patients that did not receive GO (OR:0.24, 99% CI 0.07–0.85), while this difference could not be shown for treatment with single-dose GO-1 (3 mg/m^2^) (OR: 1.0, 99% CI 0.78–1.3). Importantly, non-relapse mortality was not increased in patients treated with GO [14]. A major concern for patients receiving GO is the risk of SOS, especially among patients who received allogeneic hematopoietic cell transplantation (allo-HCT) within the preceding three months [21]. Revised dosing schedules significantly lowered rates of SOS to expected levels in patients being GO-naive [14, 22, 23]. Thus, the randomized comparison of GO-147 versus GO-1 as adjunct to intensive induction therapy appears as a logical consequence in terms of safety and efficacy [24].

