### Study setting and randomization

In Germany, patients with newly diagnosed AML are usually referred to academic Hospitals. In this study, patients will be recruited in 25 academic centers registered in the Study Alliance Leukemia (SAL) group. Participating centers are contacted by study monitors and the medical coordinator monthly to promote patient recruitment. Furthermore, after protocol amendments or upon relevant updates during the study, a newsletter will be sent to all participating centers. Conferences with the participating centers of the SAL network are done regularly to share information regarding therapy responses and complications seen within the study. Expecting at least 5 eligible patients per year and center, approximately 2 years are required to recruit the intended number of patients.

Each patient having signed informed consent and meeting all inclusion criteria is registered in the electronic case report form (eCRF). Via eCRF a unique patient ID (PAT-ID) is assigned. Following registration, eligible patients are upfront randomized 1:1 to induction chemotherapy containing either fractionated GO treatment (GO-147) or one single dose of GO (GO-1) and again 1:1 either to glasdegib or placebo (double-blinded) as adjunct to consolidation therapy and as single-agent for 6-months of maintenance therapy. Following these randomizations, 63 patients shall be allocated to each arm. Randomization is stratified by assumingly important prognostic factors age (≤70 years vs. > 70 years) and Eastern Cooperative Oncology Group (ECOG) performance status (PS) (ECOG PS = 0 vs. ECOG PS > 0). Block randomization with varying block lengths is used and performed using the web tool www.randomizer.at, by which randomization for double-blind clinical trials can easily be handled. Patients withdrawn from the trial retain their identification codes. Patients have to provide written informed consent before any protocol-specific procedures are performed. Applicable regulatory requirements, Good Clinical Practice, and ethical principles from the Declaration of Helsinki are adhered to during the study.

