### Participants

#### Inclusion criteria

Inclusion criteria are outlined in Table 3. Key inclusion criteria are newly diagnosed AML according to the 2016 WHO classification, no prior chemotherapy for leukemia except hydroxyurea for up to 7 days to control hyperleukocytosis, age 60 years and older, and ECOG PS between 0 and 2.

**Table 3 Tab3:** Inclusion and exclusion criteria

Category	Inclusion	Exclusion
Population characteristics	- Patients with newly diagnosed acute myeloid leukemia according to the 2016 WHO classification. - Genetic and immunophenotypic assessment in one of the central laboratories. - Age ≥ 60 years, no upper age limit. - ECOG performance status ≤2. - Effective contraception method.	- AML with PML-RARA or BCR-ABL1. - Patients with known active CNS leukemia. - Pregnancy and lactation. - Known or suspected active alcohol or drug abuse. - Known positivity for HIV, active HBV, HCV, or hepatitis A infection. - Severe neurologic or psychiatric disorder interfering with ability of giving informed consent.
Prior therapies	- No prior chemotherapy for leukemia except hydroxyurea to control hyperleukocytosis (≤7 days).	- Prior treatment with a smoothened inhibitor (SMOi) and/or hypomethylating agent.
Comorbidities		- Inadequate renal function. - Inadequate liver function. - Known liver cirrhosis. - History of sinusoidal. Obstruction syndrome. - Uncontrolled hypertension. - Severe obstructive restrictive. ventilation disorder. - Myocardial infarction. - Congenital long QT syndrome. - Torsades de pointes. - Arrhythmias (including sustained ventricular tachyarrhythmia). - Right or left bundle branch block and bifascicular block. - Unstable angina. - Coronary/peripheral artery bypass graft. - Symptomatic congestive heart failure (NYHA III/IV). - Cerebrovascular accident. - Transient ischemic attack. - Symptomatic pulmonary. embolism. - Bradycardia defined as < 50 bpms. - QTc interval > 470 msec. - Uncontrolled infection. - Evidence or history of severe non-leukemia associated bleeding diathesis or coagulopathy. - Patients with a “currently active” second malignancy other than non-melanoma skin cancer.
Others	- Signed written informed consent. - Ability of the patient to understand character and consequences of the clinical trial.	- No consent for biobanking. - History of hypersensitivity to the investigational medicinal product or to any drug with a similar chemical structure. - Participation in a clinical study involving an investigational drug.

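### The primary EFS model leaves out baseline genetic risk, a centrally assessed factor the article ranks as highly prognostic; the analysis stays valid and adequately powered but forgoes precision

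*Protocol article*

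**What the plan says.** The section Sample size calculation and statistics names the two primary models: "The MRD-negativity after induction therapy is analyzed using a generalized linear mixed model and EFS with a Cox regression frailty model". It then lists their covariates: "Both models are adjusted for the following fixed factors: treatment (MRD-negativity: GO-1 vs. GO-147 and EFS: glasdegib vs. placebo), age, sex, and ECOG PS", plus recruiting centre as a random factor. The one EFS sensitivity analysis it names adds the interaction between the two randomised treatments.

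Genetics is not balanced by design either. Study setting and randomization states: "Randomization is stratified by assumingly important prognostic factors age (≤70 years vs. > 70 years"), with ECOG PS (0 versus above 0) as the only other factor.

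Elsewhere the article treats genetics as important. The Background says: "Beyond age, genetic abnormalities constitute the most influential prognostic factors for survival". It adds that the share of patients with an ELN-2017 high-risk profile "increases with older age to roughly one-quarter of patients 70 years or older". Table 3 (Inclusion criteria) requires: "Genetic and immunophenotypic assessment in one of the central laboratories".

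**The concern.** The covariate list is stated in full, so this is a point about a choice made and not about detail left to an analysis plan. The list includes sex, for which the article gives no prognostic argument. It omits a pre-treatment variable that the article ranks highly and that should exist for nearly every patient.

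In a Cox model, a strong baseline predictor left out of the model becomes unexplained variation. The estimated treatment hazard ratio then lies closer to 1 than the effect within risk groups, and the test is usually less powerful than an adjusted one. Because randomisation is not stratified by genetics, a chance imbalance in risk between the glasdegib and placebo groups would also go unaddressed in the primary estimate. Adding genetics after unblinding would then look data-driven.

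**Working it through.** **Inputs from the article (Sample size calculation and statistics).** 2-year EFS 21% (placebo) and 38.5% (glasdegib); two-sided alpha 2.5%; power 85%; 24 months accrual and 24 months follow-up; exponential dropout of 5% at 2 years; unadjusted log-rank test; 178 events, 224 patients, trial size 252. For MRD-negativity: 45% versus 20%, unadjusted chi-squared test.

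**1. The plan's EFS figure.** HR = ln(0.385)/ln(0.21) = 0.6116. Schoenfeld: d = 4(z₀.₉₈₇₅ + z₀.₈₅)²/(ln HR)² = 4(2.2414 + 1.0364)²/(0.4917)² = 178 events, as stated. With hazard λ per arm, dropout hazard γ = −ln(0.95)/24 and θ = λ + γ, the event probability is (λ/θ)[1 − (e^(−24θ) − e^(−48θ))/(24θ)]. This gives 0.872 on placebo and 0.730 on glasdegib, mean 0.801. N = 178/0.801 = 222, against the stated 224, so the figure reproduces.

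**2. Unadjusted EFS power at 252.** Expected events: 252 × 0.801 = 202. Power = Φ(½√201.9 × 0.4917 − 2.2414) = Φ(1.25) = 89.5%.

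**3. Effect of adding genetic risk.** Simulation: 2,500 trials per scenario, 252 patients 1:1, Cox model, Wald test at two-sided 2.5%, with and without a three-level risk factor. Assumed, because the article does not give them: risk shares 20/50/30% and a constant hazard ratio between neighbouring risk groups (the step HR). Age, sex, ECOG PS and centre were left out. Monte Carlo error is about √(0.9 × 0.1/2500) = 0.6 points.

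With the overall 2-year rates held at 21% and 38.5%:

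| Step HR | HR unadjusted / adjusted | Power unadjusted | Power adjusted |
|---|---|---|---|
| 1.0 | 0.613 / 0.611 | 88.6% | 88.2% |
| 1.5 | 0.610 / 0.593 | 90.2% | 92.8% |
| 2.0 | 0.609 / 0.566 | 89.8% | 96.0% |
| 3.0 | 0.600 / 0.509 | 90.6% | 98.9% |

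The gains are 2.6, 6.2 and 8.3 points. If genetics carried no information (step HR 1.0), adjusting would cost nothing beyond simulation error.

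With 0.612 taken instead as the effect within each risk group:

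| Step HR | HR unadjusted | Power unadjusted | Power adjusted |
|---|---|---|---|
| 1.5 | 0.625 | 85.6% | 88.1% |
| 2.0 | 0.651 | 79.1% | 88.7% |
| 3.0 | 0.693 | 62.6% | 87.2% |

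**4. MRD-negativity.** The same exercise with logistic models, calibrated to 20% and 45%, gives power without and with genetic risk of 98.6% and 98.7% (step OR 1.5), 97.6% and 98.2% (step OR 2), and 98.3% and 99.2% (step OR 3). At 126 per group this comparison already has about 98% power, so there is almost nothing to gain.

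**5. Chance imbalance.** Assume 25% adverse risk overall (the article gives about that share only from age 70) and 126 per group. The SD of the between-group difference is √(2 × 0.25 × 0.75/126) = 5.5 points. A gap of 10 points or more has probability 2[1 − Φ(10/5.46)] ≈ 7%. With an assumed adverse-risk HR of 2.5, such a gap moves the log hazard ratio for treatment by about 0.10 × ln 2.5 = 0.09, a factor of roughly 1.10 on the HR (first-order approximation).

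**The case against.** A reader might infer that the trial is underpowered for EFS. The article does not support that. It derives 0.612 from overall 2-year rates and plans with an unadjusted log-rank test, so 0.612 is an overall effect, and on that basis power exceeds 85% without genetic risk in every scenario. The 79% and 63% arise only if 0.612 is reinterpreted as an effect within risk groups, which the article does not say.

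A reader might also infer that the planned hazard ratio is biased. It is not. The gap between adjusted and unadjusted hazard ratios is non-collapsibility: the two are different quantities. Randomisation keeps the planned test valid, and its type I error and confidence interval already allow for chance imbalance.

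A third tempting step is to extend the point to MRD-negativity, or to support it with the Background finding that "the clinical benefit is mainly restricted to patients with favorable and intermediate-risk karyotype". The prognostic ranking in the Background concerns survival, and the MRD gain is negligible. The karyotype finding is about effect modification in a trial of GO versus no GO. It would bear on an interaction or subgroup analysis, and says nothing about glasdegib.

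Finally, the listed covariates include both stratification factors, so the model is a legitimate choice. Supportive analyses with genetic risk may stand in documents not shown.

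All of this stands and limits the point to efficiency. It does not justify leaving a collected, strongly prognostic baseline variable out of a primary model whose covariates are otherwise fully specified.

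**Conclusion.** The point holds for EFS, as a worthwhile improvement and not as a flaw in validity or planned power. Under step HRs of 1.5 to 3, adjustment gains about 3 to 8 points of EFS power over a planned level of about 89% to 90%, and gives pre-specified protection against an unlucky imbalance in genetic risk.

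The direction follows from the statistical theory and from the article's own ranking of genetics. The size rests on assumed risk shares and prognostic strengths. It could be smaller in practice: age is already in the model, the article links high-risk disease to older age, and the simulation did not include age.

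**What to change.** Before unblinding, pre-specify centrally assessed ELN-2017 genetic risk (favourable, intermediate, adverse, and an unknown category) as a fixed factor in the primary EFS Cox frailty model. State that the reported hazard ratio is then conditional on genetic risk as well as on the covariates already listed. Adding the factor to the MRD model and to its imputation model is optional, for consistency.

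The cost is a wording change and two or three parameters against about 202 expected events. It needs no new data, no extra patients and no change to the randomisation.
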